# Design and rationale of the IN CONTROL trial: the effects of real-time continuous glucose monitoring on glycemia and quality of life in patients with type 1 diabetes mellitus and impaired awareness of hypoglycemia

**DOI:** 10.1186/s12902-015-0040-3

**Published:** 2015-08-21

## Abstract

**Background:**

Hypoglycemia is the main side effect of intensified insulin therapy in type 1 diabetes and recognized as a limitation in achieving glycemic targets. Patients with impaired awareness of hypoglycemia have a threefold to sixfold increased risk of severe hypoglycemia. Real-time continuous glucose monitoring may help patients with type 1 diabetes to achieve better glycemic control with less hypoglycemic episodes. Accordingly, one may hypothesize that particularly type 1 diabetes mellitus patients with impaired awareness of hypoglycemia will profit most from this technology with improvements in their quality of life. However, this has not yet been established. This trial aims to study the effect of real-time continuous glucose monitoring on glycemia and quality of life specifically in type 1 diabetes mellitus patients with established impaired awareness of hypoglycemia.

**Methods/design:**

This is a two-center, randomized, cross-over trial with a 12-week wash-out period in between intervention periods. A total of 52 type 1 diabetes mellitus patients with impaired awareness of hypoglycemia according to Gold et al. criteria will be randomized to receive real-time continuous glucose monitoring or blinded continuous glucose monitoring for 16 weeks. After a wash-out period, patients will cross over to the other intervention. The primary outcome measure is time spent in euglycemia. Secondary outcomes include (diabetes-specific) markers of quality of life and other glycemic variables.

**Discussion:**

It remains unclear whether patients with type 1 diabetes and impaired awareness of hypoglycemia benefit from real-time continuous glucose monitoring in real-life. This study will provide insight into the potential benefits of real-time continuous glucose monitoring in this patient population.

**Trial registration:**

Clinicaltrials.gov: NCT01787903.

**Electronic supplementary material:**

The online version of this article (doi:10.1186/s12902-015-0040-3) contains supplementary material, which is available to authorized users.

## Background

Type 1 diabetes mellitus (T1DM) constitutes about 10-15 % of total diabetes rates and its incidence has been increasing worldwide at an alarming rate of 3-5 % per year [1]. T1DM is associated with an increased risk of microvascular and macrovascular co-morbidities. The Diabetes Control and Complication Trial/Epidemiology of Diabetes Interventions and Complications (DCCT/EDIC) studies have shown that intensive versus conventional glycemic control results in a reduction of microvascular [2] but also macrovascular complications [3]. However, the DCCT also demonstrated that intensive treatment associates with a considerably increased rate of hypoglycemia [2]. With incidences of approximately 2 per patient per week [4–6] for mild (i.e. self-treated) hypoglycemia, and 0.1-1.5 per patient year [2, 5–9] for severe hypoglycemia (SH), hypoglycemia is both the main limitation in achieving glycemic targets and the main side effect of intensified insulin therapy in T1DM [10, 11]. The American Diabetes Association (ADA) defines SH as an event requiring assistance of a third party, with symptoms of neuroglycopenia and recovery of neurological symptoms after restoration of plasma glucose [12].

Hypoglycemia is both a physical and psychological burden [13, 14]. It can interfere with every aspect of daily life, such as sleep, exercise, driving or otherwise travelling, but also social interactions and even employment [13]. Patients worry about having episodes of SH or getting the late complications of T1DM [6], and there is always the possibility of a hypoglycemic episode leading to a coma [6]. Recurrent hypoglycemia may promote the development of impaired awareness of hypoglycemia (IAH) by decreasing the glycemic threshold in the brain required for the activation of the autonomic system [15]. Consequently, by the time the glucose level is low enough to elicit symptoms, patients fail to recognize them due to neuroglycopenia. To date, no consensus on a satisfactory definition of IAH exists. We defined IAH as the diminished ability to recognize the onset of hypoglycemia [14]. Hypoglycemia awareness can be assessed by using self-rating questionnaires. The Gold method consists of one question: “do you know when hypoglycemia is commencing?”. The state of hypoglycemia awareness is then assessed by using a 7-point visual analogue scale, with 1 representing “always aware” and 7 representing “never aware”. A score of ≥4 suggests impaired awareness of hypoglycemia [16]. The Clarke method consists of eight questions identifying the respondents exposure to episodes of (mild and severe) hypoglycemia and examining the glycemic threshold for hypoglycemia. Impaired awareness of hypoglycemia is implied if the respondent has a score of ≥4 [17]. Both scoring systems show good performance in adults [18]. Impaired awareness of hypoglycemia renders patients at a threefold to sixfold increased risk of SH which considerably hampers their quality of life [13, 16, 19]. In addition, hypoglycemia can be fatal, with hypoglycemia mortality estimates ranging from 4 to 10 percent of deaths of patients with type 1 diabetes [20, 21]. Furthermore, a recent observational study showed that T1DM patients with an glycated hemoglobin level of 6.9 % or lower had a twice increased risk of death from any cause and cardiovascular causes compared with matched controls [22].

In 2006, real-time continuous glucose monitoring (RT-CGM) was introduced to assist patients in their self-management of blood glucose [23]. Real-time continuous glucose monitoring systems measure interstitial glucose levels and provide this information every five or ten minutes, with a delay of approximately 8 to 15 minutes [24–26]. The added value lies in the display of trends and alarms that can be set to warn for impending hypo- or hyperglycemia [27, 28]. RT-CGM is associated with an improvement of glycemic control [27, 29–41] and shorter duration of hypoglycemic episodes [42–44]. However, the effect of conventional RT-CGM (i.e. without automated insulin suspension) specifically in patients with IAH has not yet been established in a real life setting [45]. In most studies either recent severe hypoglycemia was among the exclusion criteria [29] or the frequency of severe hypoglycemia at baseline was not mentioned [37, 40, 46]. Studies done in subjects with normal hypoglycemia awareness already indicate that use of RT-CGM might improve the impact of T1DM on daily life [28] and might increase treatment satisfaction [47], although an effect on the fear of hypoglycemia is not apparent [48]. Since experiencing the issues mentioned above might especially be the case for patients with IAH, it is not unlikely that use of RT-CGM might improve the quality of life in those patients.

This trial aims to study a wide range of effects of RT-CGM specifically in T1DM patients with established IAH, regardless of baseline HbA1c. We hypothesize that the use of RT-CGM, relative to a control intervention using masked CGM, will result in improvement of time spent in euglycemia and quality of life in T1DM patients with IAH.

## Methods/design

### Design

This is a two-center, randomized, cross-over trial with a 12-week wash-out period in between intervention periods (Fig. 1). Ethical approval has been granted by the medical ethical committee of the VU University Medical Center (VUMC).

**Fig. 1 Fig1:**
[figure not shown]
General study plan

### Recruitment

Subjects will be recruited from the outpatient clinic of the VUMC, Amsterdam and the Medical Center Haaglanden (MCH), The Hague, The Netherlands, from outpatient clinics at affiliated hospitals, but also from regional hospitals and via advertisements in local newspapers. Responders will be sent written extensive patient information. Written informed consent will be obtained from the subjects prior to any trial related procedure.

### Study population

Fifty-two subjects with T1DM and IAH will be enrolled. Because patients with IAH often are already in good to moderate control in terms of HbA1c, patients will be included regardless of their HbA1c.

#### Inclusion criteria

T1DM, diagnosed according to ADA criteria [49] regardless duration.Use of multiple daily injections of insulin or continuous subcutaneous insulin infusion. (Participants may not change their treatment method during the study.)Age between 18 and 75 years (inclusive).IAH according to the questionnaire by Gold et al. [16].Performing self-monitored blood glucose measurements (SMBG) at least 3/day or 21/week.

#### Exclusion criteria

History of (recent) major renal, liver, or (ischemic) heart disease (including cardiac conduction disorders).Current untreated proliferative diabetic retinopathy.Current (treatment for) malignancy.Current use of non-selective beta-blockers.Current psychiatric disorders, including schizophrenia, bipolar disorder, anorexia nervosa or bulimia nervosa.Substance abuse or alcohol abuse (men >21 units/week, women >14 units/week).Current pregnancy or intention to conceive.Current use of RT-CGM other than for short term (i.e. diagnostic use or use shorter than 3 consecutive months).Hearing or vision impairment hindering perceiving of glucose display and alarms, or otherwise incapable of using a (RT-)CGM, in the opinion of the investigator.Poor commandment of the Dutch language or any (mental) disorder that precludes full understanding of the purpose and instructions of the study.Participation in another clinical study.Known or suspected allergy to trial product or related products.

### Study plan

A detailed overview of study visits, telephone consultations and procedures is given in Additional file 1. At each visit, a recent history will be taken, including e.g. complaints, adverse events, changes in medication treatment regime and the occurrence of SH (i.e. requiring assistance of a third party). Weight and vital signs will be measured at each visit. Outcome measurements will be performed at baseline and after each 16-week intervention phase (Fig. 1).

### Screening

Hypoglycemia awareness will be assessed using the questionnaire developed by Gold et al. and by Clarke et al. [16, 17]. The frequency and severity of severe hypoglycemia will be assessed using the self-report questionnaire according to Langan et al. [50]. Subsequently, a complete medical and socio-economic history will be taken and a complete physical examination will be performed. Participants will be examined for the presence of diabetes-related (microvascular) complications. Thus, plasma creatinine, calculated estimated glomerular filtration rate (eGFR) and albumin-creatinine ratio (ACR) in a random urine sample will be measured to evaluate diabetic nephropathy [51, 52]. The presence/severity of diabetic sensorimotor polyneuropathy will be quantified by the Modified Toronto Clinical Scoring System [53]. For the assessment of vibration sense, the vibration perception threshold will be quantified using a neurothesiometer [54]. The presence/severity of diabetic retinopathy (DRP) will be assessed based on the relevant medical history and a recent (<6 months) evaluation by the patient’s ophthalmologist. In the absence of this information, patients will be either requested to visit their ophthalmologist prior to study onset or they will be referred for fundus photography [55]. Blood will be collected to ascertain in- and exclusion criteria and for baseline measurement.

### Run-in phase

A 5-week run-in phase, starting after inclusion, will be used to allow for study effects and enable diabetes- and study-related education. All participants will receive approximately 30 minutes of individual education in the principles of diabetes management, including basic principles of standardized SMBG, glucose fluctuations, insulin and carbohydrates, hyper- and hypoglycemia, impaired awareness of hypoglycemia and RT-CGM. In case a participant does not use the technique of carbohydrate counting, no education on this subject will be given in order to prevent confounding. Participants will be equipped with a masked CGM device to be worn for two weeks to gather baseline data and to familiarize them with longer-term wearing of this type of device. During follow-up visits, there will be an ongoing evaluation of diabetes self-management and knowledge of diabetes management, as this is part of standard diabetes care. A test of knowledge will not be used.

### Intervention phase

#### Randomization

After successful participation in the run-in phase, participants will be randomized, using block randomization (allocation 1:1), to the first intervention period. A sealed envelope for each participant will be drawn and opened by qualified study staff. In addition, the block size will be determined by the institutional trial pharmacist. Study staff and participants will not be blinded for treatment order, as this is an open intervention study. When allocated to RT-CGM, participants will receive additional education on how to use RT-CGM and the accompanying specialized software. Participants will be asked to upload their RT-CGM-data before each follow-up visit. When allocated to masked CGM, participants will continue to wear their CGM device from the run-in phase. Participants are encouraged to wear the assigned study devices continuously.

#### Follow-up visits and telephone consultations

During the intervention periods there will be monthly follow-up visits and telephone consultations involving inquiry after e.g. actual complaints/symptoms, episodes of (severe) hypoglycemia, study device use and related technical issues, and medication using a checklist. During both intervention periods, research physicians will guide participants in concordance with the ADA Standards of Medical Care in Diabetes [56]. The guidance will be equal during both intervention periods. During the visits, therapy adjustments will be discussed and logged, based on RT-CGM-data in the RT-CGM group or SMBG-data in the masked CGM group. No treatment or insulin titration protocol will be used, neither will SMBG use be standardized, in order to avoid additional interventions.

#### Wash-out phase

After the first intervention phase, participants will enter a 12-week wash-out phase, during which they will only receive two-weekly telephone consultations for taking recent histories and monitoring of potential adverse events. At the end of the wash-out period, general diabetes and CGM education will be given similar to the first run-in phase. Also, participants will start to wear masked CGM again for two weeks to gather baseline data for the second intervention period.

### Endpoints

#### Primary endpoint

The mean difference in time spent in euglycemia (interstitial glucose range >3.9 mmol/L - ≤10.0 mmol/L), expressed as hours/day between the two intervention periods. The specific ranges of euglycemia are based on the definition of the ADA and comparing literature [12, 44].

#### Secondary endpoints

(Diabetes-specific) markers of quality of life, as assessed with questionnaires covering: diabetes-related emotional distress (PAID-5 (Cronbach’s α = 0.86) [57]), fear of hypoglycemia (HFS-2 (Cronbach’s α = 0.94) [58, 59]), diabetes self-efficacy (CIDS (Cronbach’s α = 0.94) [60]), generic health-status (EQ5D (Cronbach’s α = 0.73) [61, 62]) and emotional well-being (Cronbach’s α = 0.82) (WHO-5 [63–65]).Other glycemic variables, including HbA1c, time spent in hypo- and hyperglycemia ranges, frequency of severe (i.e. requiring assistance of a third party) and mild (i.e. self-treated) hypoglycemia (assessed by analyzing (RT-)CGM data) and duration of hypoglycemia.Changes in hypoglycemia awareness score according to Gold et al. [16].Glycemic variability. Glucose variability (defined as inter-day and intraday glycemic variability), will be calculated as Mean Of Daily Differences and Continuous Overall Net Glycemic Action, using all (RT-)CGM values during the 16 week intervention period [66, 67].

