### Study devices

The MiniMed Paradigm® Veo™ System (Medtronic, Northridge, CA) will be used as RT-CGM device. The system consists of a continuous Enlite™ glucose sensor, a MiniLink^™^ transmitter and the Paradigm® Veo™ System [74, 75]. The sensor is a membrane-covered enzyme coated electrode placed through the skin into the subcutaneous space using an auto-insertion device. This sensor has to be changed every 6 days . The wireless MiniLink^™^transmitter is a small rechargeable device that is connected to the glucose sensor and sends glucose data wirelessly to the monitor every 5 minutes, 24 hours a day. The monitor shows real-time glucose measurements and provides information regarding changes in glucose levels (trends). Calibration is required every 12 hours. The system allows to set alarms, i.e. alarms for low and high glucose limits, as agreed with the health-care provider, at which the system should alert the patient whenever glucose values are approximating or exceeding these pre-set values. The low-glucose limit during this trial will be pre-set at 4,5 mmol/L and cannot be lowered in order to prevent hypoglycemia. Also, accuracy of glucose sensors decreases in hypoglycemic ranges [76, 77]. Low-glucose suspension function will not be used. Finally, the system shows participants their real-time glucose values and patterns, and allows for adjustment of treatment and/or lifestyle accordingly.

The masked CGM device that will be used is the iPro™2 Continuous Glucose Monitor (Medtronic, Northridge, CA), which also uses the Enlite™ glucose sensor [74, 75]. Masked CGM- and SMBG-data must be uploaded every week for the purpose of (retrospective) calibration of the iPro™2. Participants will be blinded to the CGM-data. The investigators will review the CGM-data for quality based on duration of sensor wear, number of sensor values, accuracy (mean absolute difference), number of valid calibrations. In case of missing data due to low quality CMG-data, the intervention phase will be extended.

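### Severe and mild hypoglycemia are defined by who treated the event, but the stated data source is CGM, which cannot show this

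*Protocol article*

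**What the plan says.** The entry on other glycemic variables under Secondary endpoints reads, in the relevant part: "frequency of severe (i.e. requiring assistance of a third party) and mild (i.e. self-treated) hypoglycemia (assessed by analyzing (RT-)CGM data". It gives a definition for each class and one data source after the noun that the two classes share.

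The Background uses the same definitions. The diabetes association it cites "defines SH as an event requiring assistance of a third party, with symptoms of neuroglycopenia and recovery of neurological symptoms after restoration of plasma glucose", and the article gives a rate "for mild (i.e. self-treated) hypoglycemia". On the device, the Background says: "Real-time continuous glucose monitoring systems measure interstitial glucose levels and provide this information every five or ten minutes". According to Study devices, the masked system uses the same type of glucose sensor.

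The article also describes collection by report. Under Study plan, the history taken at each visit includes "the occurrence of SH (i.e. requiring assistance of a third party". Under Follow-up visits and telephone consultations, a checklist used during both intervention periods asks about hypoglycemic episodes, including severe ones. The endpoint entry refers to neither.

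On wear, the section Randomization says participants are encouraged to wear the assigned devices continuously. The Discussion adds that continuous RT-CGM use is not mandatory.

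**The concern.** The endpoint names a measurement that does not contain the defining feature of the event. The article says something that does not fit together, so this is more than a detail left for the analysis plan.

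Three things are at stake.

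- **Meaning of the count.** If the sentence is followed literally, lows on the trace have to be sorted into severe and mild without the information that separates them. Some lows belong to neither class. The section Carry-over itself speaks of events that would otherwise go undetected, and an undetected low has been treated by nobody.
- **Comparability of the arms.** Study devices says that RT-CGM users see their values and have a low-glucose alarm, while users of the masked device are blinded to the data. The share of lows that patients notice and treat themselves could therefore differ between the arms, and the trace alone would not reveal it.
- **Completeness.** An assisted event on a day without a sensor leaves no trace. A report-based count would still capture it.

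The Background presents severe hypoglycemia as a central risk in these patients, so readers will look closely at this secondary endpoint.

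**Working it through.** The article gives no figure for this endpoint, so there is nothing to recompute. The check sets the definitions against the sources.

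1. **What each class requires.** Severe: help from another person and, by the Background definition, neuroglycopenic symptoms with recovery once glucose is restored. Mild: treatment by the patient.
2. **What CGM supplies.** A series of interstitial glucose values over time. It records no helper, no symptoms and no act of treatment. A low that resolves after the patient eats, after a relative intervenes, or without any treatment can give the same curve.
3. **Result for severe events.** None of the required elements is in the trace, so the class cannot be derived from the named source.
4. **Result for mild events.** Self-treatment is not in the trace either, so this class cannot be derived from it.
5. **How far the parenthesis reaches.** It follows the noun shared by both adjectives, so the plain reading covers both classes.
   - If it covers both, steps 3 and 4 apply. The entry also conflicts with the report-based collection of severe events under Study plan and under Follow-up visits and telephone consultations.
   - If it covers mild events only, step 4 still applies. The entry then names no source for severe events, although one is described elsewhere.
6. **Sensor wear.** Because wear is not mandatory, days without a sensor can occur. A CGM-only count has no information on those days, whereas the history and checklist cover them.
7. **Effect on the rest of the design.** The primary endpoint is time in the euglycemic range, which is properly a CGM quantity. The sample size of 52 rests on that endpoint alone. Neither changes.

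The mismatch therefore holds on both readings. The readings differ only in whether it reaches severe events.

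**The case against.** The strongest reply concerns severe events. The parenthesis comes directly after the words on mild hypoglycemia and may be meant for them only. The history under Study plan defines severe events in the same way as the endpoint, and the checklist runs through both intervention periods. Nowhere does the article give a CGM rule for a severe event. This stands to the following extent: the data for an assistance-based count should exist. A reader might infer that the trial would report a sensor-threshold count as severe hypoglycemia, but the documents do not establish that.

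A second reply is that participants log finger-prick values, meals, insulin and activities, as the Discussion mentions, and that these logs could point to self-treatment. They might help for mild events. However, the endpoint entry does not name them, they would not show third-party help, and the Discussion itself worries about compliance with logging among pump users.

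Three further arguments may tempt a reader and should not be used.

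- The screening statement, "The frequency and severity of severe hypoglycemia will be assessed using the self-report questionnaire", describes an assessment at screening. Nothing shows it to be a competing source for the endpoint.
- Study devices says that "accuracy of glucose sensors decreases in hypoglycemic ranges". It does not say that accuracy is worst there, and the limitation is not specific to the severe and mild labels.
- The Background event rates cannot be turned into a size for this problem. The mild rate refers to self-treated episodes and cannot stand in for CGM lows. The article also supports no figure for the share of lows that would be mislabelled.

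Finally, the exact glucose threshold and minimum duration of a CGM episode may well be in the full protocol or analysis plan. Their absence from the article is not criticised here.

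**Conclusion.** The point holds as a mismatch between definition and source in a secondary endpoint. For mild events it holds on any reading. For severe events it holds on the plain reading, where the entry also conflicts with the collection of severe events by report. On the narrower reading, what remains for severe events is that the endpoint entry does not name the source that the article describes elsewhere.

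The conclusion assumes only that a series of interstitial glucose values, taken alone, does not identify who treated an event or whether it was treated. No numerical size is claimed. The text should be corrected because it is wrong as it stands and the better data are already being collected.

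**What to change.** Replace the single phrase under Secondary endpoints with two separate items:

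- Severe hypoglycemia (third-party assistance): number of events per patient per intervention period, taken from the visit history and the visit and telephone checklist, for all days regardless of sensor wear.
- CGM-detected low-glucose episodes: number relative to sensor time, by a definition set in advance in the full protocol or analysis plan, without severe or mild (self-treated) labels.

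If the investigators still want a count of self-treated episodes, they should name a report-based source for it.

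The cost is a change of wording. The history and checklist are already part of the visits and telephone consultations, and no new data, patients or device changes are needed for the two items above.
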